### Primary and Secondary Outcomes

#### Behavioral and Clinical Assessments

The primary outcome of this study will be hand gesture performance, which will be assessed with the Test of Upper Limb Apraxia (TULIA) (77). TULIA includes 48 items in two domains: Imitation (following demonstration) and pantomime (after verbal command). The test has three semantic categories of gestures: communicative (intransitive), object-related (transitive), or meaningless. Item ratings range from 0 to 5. If the participants make content errors (e.g., perseverations, substitutions), they will get 0–2 points per item. If the participants make spatial or temporal errors, they will get 3–4 points. Perfect performance equals 5 points, which is the maximum score per item. The highest TULIA total score is 240. A cutoff score will be used to measure gesture deficits in schizophrenia with < 210 TULIA total score (17). Gesture performance will be recorded on video and later evaluated by an independent examiner who is blinded to the groups or timing of the assessment. We will assess gesture performance using TULIA at four different time points (see Table 3).

**TABLE 3 T3:** Time-points of assessments.

	Screening	Baseline	Week 2 tests	Week 8 tests	Follow-up
TIME (week)	–4 to 0	0	2	8	32
**Enrollment**					
Eligibility screening	**X**				
Informed consent	**X**				
Allocation	**X**				
**Interventions**					
Real and sham brain stimulation					
Real and sham group therapy					
**Assessments**					
Gesture tests	**X**	**X**	**X**	**X**	**X**
Clinical rating scales	**X**	**X**		**X**	**X**
Community functioning		**X**		**X**	**X**
Neuroimaging		**X**		**X**	

Secondary outcomes will include additional nonverbal communication, cognitive, clinical, and functional assessments, as well as self-reports. Nonverbal communication will be tested with the Profile of Nonverbal Sensitivity (PONS) (78) assessing nonverbal social perception, and the modified postural knowledge task (79, 80) measuring gesture perception. Together, TULIA, PKT, and PONS assess nonverbal communication, as they include the *production*, the *recognition*, and the *interpretation* of gestures. History of symptoms and medication in patients will be assessed with The Comprehensive Assessment of Symptoms and History (CASH) (81). Self-reports, clinical scales, motor scales, cognitive tests and functional assessments are listed in Table 4.

**TABLE 4 T4:** Primary and secondary outcomes.

Assessments		References
Self-reports	Brief Assessment of Gestures (BAG)	(95)
	Self-report of negative symptoms (SNS)	(96)
	The satisfaction with therapy and therapist scale-revised (STTS-R) for group psychotherapy	(97)
Psychopathology	Positive and negative syndrome scale (PANSS)	(98)
	Brief negative symptom scale (BNSS)	(99)
	Thought and language disorder (TALD)	(100)
	Frontal assessment battery (FAB)	(101)
	Bern psychopathology scale (BPS)	(102)
Motor scales	Neurological evaluation scale (NES)	(103)
	Bush Francis catatonia rating scale (BFCRS)	(104)
	Salpêtrière retardation rating scale (SRRS)	(105)
	Unified Parkinson’s disease rating scale (UPDRS)	(106)
	Abnormal involuntary movement scale (AIMS)	(107)
Behavioral tests	Postural knowledge test (PKT)	(79)
	Profile of nonverbal sensitivity (PONS)	(78)
	Coin rotation	(108)
	Test of Upper Limb Apraxia (TULIA)	(77)
Neuro- and social cognition	Mayer-Salovey-Caruso Emotional Intelligence Test (MSCEIT)	(109)
	Digit span backward (DSB)	(110)
	Test of nonverbal Intelligence (TONI)	(111)
	EMOREC-B	(56)
	Hinting task (HT)	(112)
	EmBODY tool	(113)
Functional assessments	Global assessment of functioning (GAF)	(88)
	Social and occupational functioning assessment score (SOFAS)	(114)
	Personal and social performance (PSP)	(114)
	University of California, San Diego performance-based skills assessment brief (UPSA-b)	(115)
	Social level of functioning (SLOF)	(116)

**FIGURE 2 F2:**
[figure not shown]
Three fMRI gesture tasks—experimental setup. **(A) Gesture planning/performance task** with the modified Test of Upper Limb Apraxia (TULIA). Participants will be presented with 20 hand gestures in a random order (e.g., wave good-bye) and 10 control sentences with no gesture performance expected (e.g., “the airline flight is delayed”). Each trial will start with an instruction (3 s), followed by a triangle (planning phase: 3 s), then a 3–10 s interstimulus interval with a fixation cross (3–10 s), a circle (execution phase: 3 s), another 3–6 s interstimulus interval, and then a new gesture of the next trial is presented. **(B) Gesture perception task** with the modified Postural knowledge task (PKT). Each trial will start with a fixation cross (3–10 s) followed by a picture (max. 5 s) where the hand of the presented figure will be removed. Participants’ task is to choose the correct hand gesture provided below using button presses of a hand pad inside the scanner (1, 2, and 3) and respond while the picture is still displayed. In the example provided the correct gesture is number two. **(C) Gesture interpretation task** with point-light displays (PLD). Each trial will start with a fixation cross (3–10 s) followed by a PLD video, after which a question mark will be displayed (3 s). The video will include two PLD figures: one on the right side and the other on the left side of the screen. During the video, one PLD will perform a gesture while the other PLD will either follow or imitate these performed gestures. Participants’ task will be to indicate with the button press of a hand pad which of the two PLD figures (left or right) is imitating or following the gestures of the other when the question mark will be displayed. The gray connecting lines and the two gray circles (i.e., PLDs’ heads) are a visual aid and will not be present in the actual experiment.

Outcomes will be measured during four different time points: baseline, after cTBS (week 2), after SCRT (week 8) and follow-up (week 32) (see Table 3). At baseline, week 8 and week 32, the primary and all secondary outcomes will be tested. At week 2, the primary and a few secondary outcomes (i.e., nonverbal communication and clinical assessments) will be measured. Additionally, at baseline and week 8, neuroimaging data will be acquired to test the neural effects of the treatments.

#### Magnetic Resonance Imaging Measurements

Neuroimaging will include structural T1, arterial spin labeling (ASL), diffusion tensor imaging (DTI), blood oxygenation level dependent (BOLD) resting state and fMRI tasks. MRI acquisition will be performed at a 3T SIEMENS MAGNETOM Prisma at the Swiss Institute for Translational and Entrepreneurial Medicine (SITEM), Bern, Switzerland. We will use a 20-channel radio-frequency head coil (Siemens, Germany) for all acquisitions.

##### Functional Magnetic Resonance Imaging and Tasks

We will administer three different fMRI tasks to assess gesture planning/execution, perception, and interpretation (see Figure 2). First, gesture planning and performance will be assessed with an adapted version of the gesture task created by Stegmayer et al. (39) and Kroliczak and Frey (82). In an event related design, participants will be presented with 30 gestures in a random order: 10 meaningless (e.g., “raise your thumb and your index finger”), 10 meaningful gestures (e.g., “wave good-bye”) and 10 control sentences with no gesture performance expected (e.g., “the weather is bad”). Second, we will use the Postural Knowledge Task (PKT) (15, 26, 80) to assess participants’ gesture perception. Participants will be presented with pictures of people performing gestures (20 trials), while the hands executing those gestures are missing. Participants will be asked to choose the correct hand gesture from three choices provided. In the control condition (20 pictures), participants will be asked to indicate if the person performing the gesture is either male or female. Third, we will use the point-light-display (PLD) method to assess dynamic gesture perception. Here, human biological movements will be depicted by 12 point-light dots on the main joints of a human actor in the absence of any other visual characteristics (83–85). For our task, 40 videos of one PLD agent will be shown to perform different communicative gestures while the other PLD agent imitated/followed these performed gestures (26, 86). Participants’ task will be to identify which PLD was imitating/following the other.

### Allocation and Randomization

Interventions will start in blocks as soon as 6–8 participants can be randomized to three groups: Group A, group B or group C (see Figure 1). Patients will not know which treatment they receive; they will be allocated to one of three treatment arms in a blinded manner.

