**FIGURE 1 F1:**
[figure not shown]
Study Setup. We will randomize 72 schizophrenia patients in three different groups (24 patients per group). Group A will receive real cTBS and real SCRT. Group B will receive sham cTBS and real SCRT. Group C will receive no cTBS and sham SCRT. Both sham treatments are inactive interventions that mimic as closely as possible the real treatments. Group A and B will receive 10 cTBS sessions during the first two weeks of intervention. Additionally, Group A–C will receive 16 SCRT sessions for eight weeks. Outcomes will be measured during four different time points: baseline, after cTBS (week 2), after SCRT (week 8) and follow-up (week 32). We will also include a fourth group consisting of 24 healthy controls, who will be assessed twice (baseline and week 8) without any intervention in between.

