#### Implementation of Real/Sham Social Cognitive Remediation Therapy

Real/sham SCRT will be conducted bi-weekly for 8 weeks, totaling 16 sessions of 90 min. Each group will consist of six to eight patients led by a head-therapist (VC) and a co-therapist (FW). INT-expert (DM) will train both therapists and supervises the course of the sessions.

For this trial, we will tailor an SCRT based on the INT manual (58, 59). This SCRT will include the entire social cognitive part of the original INT (consisting of a minimum of 30 sessions) and two INT neurocognitive modules. As such, we will use psychoeducation and Cognitive Behavioral Therapy for Psychosis (CBTp) techniques. This intervention will have the main goal of improving gesture deficits in schizophrenia and will be separated in five blocks; each including neuro- and social cognitive MATRICS-domains (see Table 2). The first, third and fifth block will focus predominantly on using and interpreting nonverbal cues in social contexts. The second and fourth blocks will address memory and attention, both of which are essential for functioning in social interaction. Three sessions will be dedicated to each block, totaling 15 sessions overall. With each session, the content of the blocks will increase in complexity. A final 16th session will be added, in which the content delivered in all previous five blocks will be summarized.

**TABLE 2 T2:** SCRT therapy contents a trained cognitive processes.

	Introductory session: Psychoeducation topics	Training session: Compensation and restitution sessions with interactive and computerized exercises	Transfer session: Practicing coping strategies in daily life with homework
*Block 1:* *Emotion perception and expression*	Six basic emotions: their function, their expression (e.g., gestures) and their effect on perception/attention	Affect recognition and affect expression	Practicing newly learned affect recognition strategies with their regular environment
*Block 2:* ** *Verbal/visual learning and memory* **	Short term memory, long term memory and prospective memory	Mnemonic strategies (e.g., chunking, external memory aids such as calendars and post-its)	Practicing familiar and newly learned mnemonic strategies

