### Statistical Considerations and Plan

Assuming a medium effect size (*f* = 0.15) in a repeated measures ANOVA with moderate-high correlation between time points (0.75), a power of 0.95 and an alpha = 0.05, we will need 72 patients (24 per group). In addition, a control group of 24 healthy subjects will be required. All four groups will be compared pre-to-post with an interval of 8 weeks (see Figure 1). The main effects of the combined interventions on the primary and secondary outcomes will be calculated in a repeated measures design including 3 main time points (Baseline, week 2, and week 8) and three patient groups (A, B, and C). With the latest SPSS and R versions, we also will run additional (partial) correlations, linear regressions, MANCOVAS using covariates (e.g., age, education, and medication).

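### All three arms are treated in therapy groups, but the sample size and the stated analysis treat the 72 patients as independent; the batch and group-size rules also need reconciling

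*Protocol article*

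**What the plan says.** In the section Implementation of Real/Sham Social Cognitive Remediation Therapy, both the real and the sham programme run for 16 sessions of 90 minutes over eight weeks, and "Each group will consist of six to eight patients led by a head-therapist". The Figure 1 legend confirms that arms A, B and C all attend. Arms A and B receive the same real programme; the article does not say whether they sit in the same therapy groups.

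Allocation and Randomization says: "Interventions will start in blocks as soon as 6–8 participants can be randomized to three groups". The Figure 1 legend says: "We will randomize 72 schizophrenia patients in three different groups (24 patients per group").

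Statistical Considerations and Plan sizes the trial with "Assuming a medium effect size (*f* = 0.15) in a repeated measures ANOVA", "moderate-high correlation between time points (0.75") and "a power of 0.95 and an alpha = 0.05, we will need 72 patients (24 per group"). Effects are to be estimated "in a repeated measures design including 3 main time points (Baseline, week 2, and week 8) and three patient groups (A, B, and C"). That section mentions no therapy group, start batch, ICC or design effect.

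**The concern.** Patients who spend eight weeks in the same interactive sessions are likely to change together to some degree. If they do, an arm mean is less precise than 24 independent patients would make it. An analysis that ignores this gives standard errors that are too small, p-values that are too low and a power figure that is too high. The contrasts that compare different therapy groups are affected: always those with arm C, and also A vs B if A and B are treated apart.

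The size of the effect depends on who sits with whom, and here the article is unclear. The start rule and the group-size rule do not fit on their plain reading, so a reader cannot tell which clustering structure the trial has.

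**Working it through.** **1. The plan's own figure.** Inputs from Statistical Considerations and Plan: f = 0.15, correlation ρ = 0.75, alpha 0.05, three arms, m = 3 time points. For the arm-by-time interaction with independent patients:

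- λ = f² × N × m / (1 − ρ) = 0.0225 × 72 × 3 / 0.25 = 19.44
- degrees of freedom (3 − 1)(3 − 1) = 4 and (72 − 3)(3 − 1) = 138
- power from the noncentral F = 0.952; at N = 69 it is 0.943

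So 72 is the smallest multiple of three that reaches 0.95, and it contains no allowance for clustering.

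**2. Design effect.** DE = 1 + (s − 1) × ICC, with s the therapy-group size. The article gives no ICC, so 0.02, 0.05 and 0.10 are assumed, as a share of the variance of change from baseline to week 8. With arm-specific groups, 24/8 = 3 to 24/6 = 4 groups make up an arm.

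**3. Arm-specific groups.** When groups are ignored, the between-arm mean square is inflated by DE and the within-arm mean square shrinks to (24 − DE)/23. The F ratio is too large by c = 23 × DE / (24 − DE), and the true error of a three-arm test on change is P(F(2, 69) > 3.130/c). For ICC 0.05 and groups of six: DE = 1.25, c = 28.75/22.75 = 1.264, 3.130/1.264 = 2.48, error about 9.2%.

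**4. A and B share real-SCRT groups,** with h = s/2 patients from each arm. Within A or B the design effect is DE_h = 1 + (h − 1) × ICC.

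- A vs B: the shared group effect cancels, so c = (1 − ICC) × 23 / (24 − DE_h). For ICC 0.05 and s = 6: DE_h = 1.10, c = 0.95 × 23/22.90 = 0.954, error about 4.5%.
- A vs C: the average design effect is (1.10 + 1.25)/2 = 1.175, c = 1.175 × 23/22.825 = 1.184, error about 7.1%.
- The overall test was simulated with no treatment effect.

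| Assumed ICC on change | 0.02 | 0.05 | 0.10 |
|---|---|---|---|
| DE, groups of 6 / 8 | 1.10 / 1.14 | 1.25 / 1.35 | 1.50 / 1.70 |
| Error, three-arm test, arm-specific groups of 6–8 | 6.6–7.2% | 9.2–11.0% | 13.8–17.6% |
| Error, three-arm test, A and B share groups of 6–8 | 5.7–5.9% | 6.7–7.7% | about 8.5–10.4% |
| Shared groups: A vs B | 4.7–4.8% | 4.5–4.6% | 4.0–4.1% |
| Shared groups: A vs C | 5.8–6.2% | 7.1–8.0% | 9.1–11.1% |
| Error, three-arm test, arm-specific groups of 2–3 | 5.3–5.6% | 5.8–6.6% | 6.6–8.3% |
| Power at N = 72, arm-specific 6–8 (λ/DE) | 0.93–0.92 | 0.89–0.86 | 0.82–0.76 |
| Same, degrees of freedom counted from groups | 0.86–0.79 | 0.80–0.71 | 0.72–0.59 |

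The scale of the ICC matters. At ρ = 0.75, change has only 2 × (1 − 0.75) = 0.5 of the variance of a single score. An ICC quoted as a share of week-8 variance therefore does more damage: the full 3 × 3 test, simulated at 0.05 on that scale with arm-specific groups of 6–8, runs at 11.7–14.7%.

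**5. The two size rules.** Six to eight people split over three arms give 2–3 per arm. If A and B sit together, the real group has 4–6 members and the sham group 2–3. One split (8 as 3/3/2) just reaches six for real SCRT, but leaves two for sham. No split of one such batch fills both kinds of group to six. The rules agree if 6–8 means per arm (a pool of 18–24), or if a whole batch goes to one arm.

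**The case against.** The strongest case against has four parts.

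- **No ICC is given, and it may be small.** The same two therapist roles lead the groups from a script, and the primary outcome is an individual test rated from video by a blinded examiner. This stands as a limit on size: at ICC 0.02 the error is at most about 7%. It does not make the ICC zero.
- **Model details may sit in an analysis plan that is not shown.** This stands for random effects and degrees of freedom. It does not reach the sample-size calculation, which the article states in full.
- **The inflation depends on group composition.** This stands. With shared A/B groups, A vs B is not inflated; with groups of 2–3 the effect is small unless the ICC is near 0.10.
- **The size rules may be loose wording rather than conflict.** Partly. Reading 6–8 as per arm resolves it, but the text does not say so.

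Two stronger readings are tempting. A reader might infer that whole batches are allocated to one arm, so that the trial rests on 9–12 clusters and the pandemic interruption is confounded with arm. The article does not say this: the Figure 1 legend and Allocation and Randomization both speak of randomising or allocating patients. Calendar confounding would arise only under whole-batch allocation.

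A reader might also infer that the mismatch in the size rules itself raises the error rate. It does not; unmodelled therapy groups do. A batch effect shared by all arms, with every batch split across them, makes the 3 × 3 test conservative (4.0% and 3.4% at 0.05 and 0.10 of week-8 variance).

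**Conclusion.** The concern holds in conditional form. Two things are firm: the stated N = 72 has no allowance for therapy groups although every arm is treated in groups, and the start rule and the group-size rule do not fit as written.

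The effect on the error rate is conditional on an assumed ICC and on group composition. At ICC 0.05 on change, the nominal 5% three-arm test runs at about 9–11% with arm-specific groups of six to eight, and about 7–8% if A and B share groups. At ICC 0.02 it is about 6–7% in either case. Stated power of 0.95 becomes about 0.86–0.89 at ICC 0.05 with arm-specific groups, or 0.71–0.80 with degrees of freedom counted from groups. These figures take equal group sizes, 24 patients per arm and no dropout.

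**What to change.** - **Reconcile the two sections.** State whether 6–8 is per batch or per arm, confirm that patients rather than batches are the unit of randomisation if that is so, and say whether A and B share real-SCRT groups.
- **Primary model.** Add a therapy-group random effect with Kenward–Roger degrees of freedom. Include start batch as a factor where batches contain all three arms. Where A and B share groups, estimate A vs B within therapy group.
- **Power.** Give the ICC range assumed and restate power at N = 72 over that range. No additional enrolment is needed for this.

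Cost: a change of wording and one or two model terms, provided that group and batch membership have been recorded, which the article does not state. The real price is statistical. Contrasts between therapy groups will have wider intervals and lower stated power. With 9–12 arm-specific groups, only 9 − 3 = 6 to 12 − 3 = 9 degrees of freedom separate groups within arms. If A and B share groups, A vs B loses little.

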## Methods

### Aims and Hypotheses

This study’s main goal is to determine the effects of combined cTBS over rIPL and SCRT on gesture performance and social functioning in patients with schizophrenia. In addition, we aim to investigate neurocognitive, social cognitive, motor, clinical and neural effects of both interventions as secondary outcome measures. As cTBS enhances neuroplasticity and improves use of neural resources (46, 74), we expect administration of cTBS to facilitate SCRT training effects. Additionally, we hypothesize that the expected improvement of gesture performance will have positive effects on functional outcome, as both have been reported to be linked in schizophrenia (20). At the neural level, we hypothesize that the brain activity of patients will converge to the brain activity of healthy controls after both interventions, especially within the praxis network (39, 40).

This randomized controlled trial (RCT) will include three patient groups (see Figure 1). First, group A will receive real cTBS and real SCRT. Second, group B will receive sham cTBS and real SCRT. Third, group C will receive no cTBS and sham SCRT. In this study, we will also include a fourth group consisting of healthy controls, who will be assessed twice without any intervention in between. We expect the combination of cTBS and SCRT to show positive effects on both primary and secondary outcomes in patients with schizophrenia spectrum disorders. As such, we expect group A to have superior performance over group B and C in gesture performance and functional outcome after intervention (A > B > C).

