### Advantages

The design of this RCT encompasses numerous advantages. The main strength of our study is the *combination* of two interventions; coupling brain stimulation with group therapy may exert cumulative therapeutic effects in gesturing and functioning in schizophrenia (20). Additionally, cTBS enhances neuroplasticity in schizophrenia patients (46, 74) and thus, may facilitate SCRT training effects. Thanks to the two comparators (sham cTBS and sham SCRT) we can evaluate the therapeutic effects of both interventions on behavioral, clinical, and neural levels. Also, we may find insights to predictors of treatment outcome. Further, the RCT design allows elimination of selection bias in treatment assignment and enables blinding from assessors and participants. Moreover, by collecting detailed demographic information over time, we will be able to correct for age, gender, education and antipsychotic medication dosage. Longitudinal data allows exploration of change in our patients, and thus, gives insight on the longevity of treatment effects. For example, our design may shed light on factors that are essential for the transfer of coping strategies. Most importantly, we are running one of the very few RCT on SCRT to involve acquisition of neuroimaging data before and after intervention. We can directly compare neural alterations to potential behavioral changes after the interventions. If this study proves to be successful it has the potential to be beneficial for other psychiatric disorders, which exhibit similar socio-cognitive dysfunctions such as depression (93, 94).

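### Group C has neither real nor sham cTBS, so full patient blinding can hold only between groups A and B, and no contrast isolates the effect of SCRT

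*Protocol article*

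**What the plan says.** Aims and Hypotheses defines the arms. Group A has both active treatments; group B has the placebo coil together with the active group therapy. The last arm is set out as follows: "Third, group C will receive no cTBS and sham SCRT". On stimulation, Figure 1 adds: "Group A and B will receive 10 cTBS sessions during the first two weeks of intervention". All three arms have 16 group-therapy sessions over eight weeks.

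Study Design calls the trial three-arm, double-blind and sham-controlled. Allocation and Randomization states, without separating the arms: "Patients will not know which treatment they receive; they will be allocated to one of three treatment arms in a blinded manner". The Advantages section of the Discussion says that the design enables blinding of assessors and participants, and goes on: "Thanks to the two comparators (sham cTBS and sham SCRT) we can evaluate the therapeutic effects of both interventions".

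Aims and Hypotheses predicts the order A > B > C for gesture performance and functional outcome. It also gives the reason for combining the treatments: "we expect administration of cTBS to facilitate SCRT training effects". Under Primary and Secondary Outcomes, the TULIA is scored from video by an independent examiner who is blind to group and to the timing of the assessment.

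**The concern.** A patient who never has a coil session knows that he or she receives no stimulation, whatever else is disclosed. A blinding statement that covers all three arms therefore conflicts with the arm definitions.

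The same feature affects interpretation. The predicted ordering makes B versus C part of the main hypothesis, and all three arms enter the main repeated-measures analysis. If C does worse than B, the text as it stands invites the reader to take this as a double-blind, sham-controlled effect of SCRT. Part of the difference could instead come from attending stimulation sessions, or from knowing that one is not stimulated. The gesture test depends on the patient's effort, and Table 4 includes self-reports. A blinded video rater protects the scoring of the TULIA but not what the patient does or reports.

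**Working it through.** **The plan's own figure.** The sample size is not in dispute. For the group-by-time interaction with f = 0.15, correlation 0.75, N = 72, three groups and three times (Statistical Considerations and Plan), assuming sphericity: noncentrality = f² × N × m / (1 − ρ) = 0.0225 × 72 × 3 / 0.25 = 19.44. With 4 and 138 degrees of freedom at alpha 0.05, power is 0.952, and 72 is the smallest multiple of three that reaches 0.95. This is an overall test; it does not say which contrast drives a result or what that contrast measures.

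**What each arm receives** (Aims and Hypotheses; Figure 1; Interventions).

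| Arm | Stimulation | Group therapy | Sessions |
|---|---|---|---|
| A | real cTBS | real SCRT | 10 + 16 = 26 |
| B | sham cTBS | real SCRT | 10 + 16 = 26 |
| C | none | sham SCRT | 0 + 16 = 16 |

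**What each contrast estimates.** In a simple additive description, let c be the direct effect of real over sham cTBS, s the effect of real over sham SCRT, i any extra gain when cTBS and SCRT are combined, and p the effect of attending stimulation sessions and believing one may be stimulated, against knowing one is not. Relative to C:

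- A = c + s + i + p
- B = s + p
- C = 0

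The contrasts are then:

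- A − B = c + i: one component changes, with the same visits and the same therapy. This is the effect of cTBS added to SCRT.
- B − C = s + p: two components change.
- A − C = c + s + i + p: everything changes.

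Three arms give two independent contrasts for four unknowns. Reading B − C as SCRT requires p = 0, which the design does not secure. Separating i from c would need an arm with real cTBS and sham SCRT, and there is none.

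**Who can be blind to what.** Patients in A and B all have coil sessions and all have real SCRT, so concealment of real versus sham cTBS between them is possible. Patients in C have no coil sessions. In this design the absence of stimulation always goes with sham SCRT, but whether a patient could draw that inference depends on what was disclosed at consent, which is not shown.

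**Extra exposure in A and B.** Stimulation: 10 × 17 min = 170 min. Group therapy, the same in every arm: 16 × 90 min = 1,440 min. Ratio: 170 / 1,440 = 11.8%. Each 17-minute session includes a 15-minute break.

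**At week 2.** Sixteen therapy sessions in eight weeks is two a week. If therapy starts together with stimulation (an assumption), about 4 therapy sessions are done by week 2, so B has had about 14 sessions and C about 4.

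**The case against.** The strongest defence is that the trial's stated goal is the effect of the combined treatment, and that its protections are substantial. A versus B is a clean sham-controlled comparison. The TULIA rater is blind to group and timing. Sham SCRT has the same number, length and group size of sessions as real SCRT and takes place in an interactive setting. All of this stands. It is why B versus C should not be called an open comparison, which a reader might infer: patients in C know they have no stimulation, but nothing in the document shows that they know their group therapy is the sham version.

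A second defence is the week-2 assessment. Stimulation ends then and the therapy schedule is the same in all arms afterwards, so B minus C at week 2 and the later change give some information on the stimulation-visit component. This stands in part. Therapy sessions also fall in the first two weeks if the two start together, and expectancy may persist, so the separation is not clean.

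A third concerns facilitation. A reader might infer that the article claims to test whether cTBS facilitates SCRT. It does not: Aims and Hypotheses states an expectation, and the Discussion says only that cTBS may do so. The lack of a fourth arm therefore contradicts no stated claim; it limits what may later be concluded.

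**Conclusion.** The point holds. The patient-blinding sentence and the unqualified double-blind label describe a property that the design has in full only between A and B. The claim that two sham comparators allow both interventions to be evaluated holds for cTBS added to SCRT and fails for SCRT. This follows from the arm definitions alone and needs no outside assumption.

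The measurable size is ten sessions, about 170 minutes on top of 1,440. A reader might want to turn this into a percentage of the planned B–C effect or an inflated false-positive rate. The documents do not support that: they give no expectancy or contact effect, and they state only the order of the arms, not their spacing. The blinding of the TULIA rater, the A versus B contrast and the sample size of 72 are untouched.

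**What to change.** - In Allocation and Randomization, replace the blanket sentence: patients are blinded to real versus sham cTBS between A and B; patients in C are not blinded to the absence of stimulation; the TULIA video rater is blinded to group and timing throughout. Qualify the double-blind label in Study Design and the participant-blinding statement in Advantages to match.
- Name A versus B as the only fully sham-controlled, patient-blinded contrast, estimating the effect of cTBS added to SCRT.
- Describe B versus C and A versus C as partially blinded package comparisons that include attendance at stimulation sessions, and do not attribute a B–C difference to SCRT alone. Amend the claim about the two comparators accordingly.
- Present facilitation of SCRT by cTBS as the rationale for combining the treatments, not as a conclusion the trial can test.

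The cost is wording and a narrower conclusion. With 65 patients recruited by June 2022 the arms are set, and none of these changes alters treatment, visits or sample size.
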